## DATA HANDLING AND ANALYSIS

### **Data analysis plan, including statistical methodology and planned tables and figures**

SAS 9.3 (Cary, NC) as well as the WHO drug efficacy tools provided at <http://www.who.int/malaria/toolsformonitoring.html> will be used for data management and analysis. Data will be analyzed using two methods: **per protocol analysis**, where patients who were withdrawn from the study or who were lost to follow-up are excluded, and **survival analysis**, where all enrolled patients are included in the analysis until the last day before drop-out. In addition to voluntary withdrawals or treatment non-compliance, patients will be considered for the analysis as withdrawn if the PCR results are unclassifiable.

The final analysis will include:

- A description of the patients screened, and the distribution of the reasons for exclusion.
- A description of the patients included in the study.
- The proportion of patients lost to follow-up or withdrawn and the distribution of reasons for withdrawal.
- The proportion of treatment failures in each Pv arm at day 28 and day 42 with 95% confidence intervals using both methods of analysis.
- Frequency of side effects, severe malaria, anemia, and hospitalizations by treatment arm.
- Comparison in absolute means and relative changes in hemoglobin concentration during follow-up after treatment
- Comparison of number of recurrent parasitological vivax episodes after initial parasite episode.

**Data collection:** Data will be collected and recorded at the health facility by one of the trained staff members. All data entry forms will be checked for completeness. Laboratorians may complete brief reports on laboratory findings to share with clinicians who will transfer these results to the case report form of the appropriate patient, the laboratory results will be entered into an Excel database.

**Information management and analysis software:** Microsoft Excel (Redmond, Washington) will be used for double entry of laboratory data and clinical data. SAS 9.3 (Cary, NC) will be used for data analysis.

**Data entry, editing, handling, storage and disposition:** Some open-ended data including the names of specific drugs or diagnoses will be coded prior to data entry. A list of standard codes for these fields will be developed by hand once collection of data is complete. All forms will then be coded and checked by 2 different team members.

Data will be double entered using Microsoft Excel (Redmond, Washington). Systematic routines will be developed to check for data entry discrepancies and range and consistency. All discrepancies will be resolved by reference to the original checked data collection forms. The final data set will be transformed to SAS for analysis and will no longer contain any personal identifying information.

Original data collection forms will be handled only by staff members and kept under locked storage until completely coded, checked and transported for data entry. Once data entry and cleaning are

complete the original forms will be stored under lock and key at ICAP until final analyses and reports have been prepared. They will then be destroyed.

**Storage of specimens:** Specimens obtained in this study will be saved only for the duration of molecular testing and drug testing of treatment failures and then destroyed. No samples will be stored. Specimens will not be tested for HIV.

**Quality control/ assurance:** Site supervisors will check data collection forms at the end of follow-up for completeness and accuracy of recording.

**Bias in data collection, measurement and analysis:** Some bias may be introduced through the fact that both treating clinicians and parents will be aware of which treatment a subject received; as much as possible we will rely on objective measures of improvement (fever resolution, malaria parasitemia) which will be unaffected by knowing the treatment allocation. In addition, the microscopists reading the slides will be blinded to the treatment allocation. Other biases in data collection will be minimized by use of standardized data collection instruments.

**Limitations:** Results from this study may not be applicable to other ACTs or other Pv-endemic areas with different resistance patterns. The health facilities will not be chosen randomly and thus may not be representative of our target population.

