### Specific Objectives

#### Phase 1:

- 1) **Efficacy:** To measure the clinical and parasitological efficacy of AL, CQ, AL+PQ, or CQ+PQ for *P. vivax* infection during a 42-day follow-up period. (See Annex I for WHO definitions of *P. vivax* treatment failures)
- 2) **Safety:** To compare changes in hemoglobin concentration following vivax infection in patients receiving PQ versus patients who don't receive PQ.

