**Sampling, sample size and statistical power****Sample size determination:**

The design of the study is to compare the addition of PQ to AL or CQ alone. From our previous efficacy study, CQ alone showed a success rate of 68% at day 42 (null hypothesis). It will be assumed under the alternative hypothesis that the addition of PQ will decrease the chance of relapse by at least 60% resulting in a success rate of 87%. Group sample sizes of 97 in each group will achieve 90% power to detect a difference between group proportions of 19% using the two-sided Z-test with pooled variance test statistic. The significance level of the test was targeted at 0.05. Adjusting the alpha level to 0.025 for multiple comparisons will increase the sample size to 118 in each group. The AL arm showed even a lower efficacy at day 42 in our previous study of 58%. Using this lower success rate of 58% seen with AL at day 42, resulted in a smaller required sample size of 68. Taking into account 10-20% loss to follow-up at 42 days, a sample size of 120 subjects for each treatment was determined to be optimal.

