### **Laboratory Evaluations:**

2. Urine pregnancy test will be conducted on all women aged 13-49 and anyone testing positive will be excluded.
3. Those enrolled will have a second finger prick performed to assess for the following:
  - Thin smear will be used to verify parasite species and thick smear to conduct a formal parasite count. Two qualified microscopists will read all the slides independently. Blood smears with discordant results (differences between the two microscopists in species diagnosis, in parasite density of > 50% or in the presence of parasites) will be re-examined by a third, independent microscopist, and parasite density will be calculated by averaging the two closest counts.
  - Hemoglobin measurement (HemoCue™ Hb 301HemoCue, Angelholm, Sweden) will be carried out and those with hemoglobin <8g/dL will be excluded.
  - Filter paper will be obtained for the purpose of genotyping to differentiate identical vs. different genotypes, potential molecular testing for resistance markers, and gametocyte testing. G6PD testing using the NADPH fluorescent spot test will be conducted at the end of each day. The NADPH fluorescent spot test is a qualitative test and those determined to be G6PD deficient will not be given primaquine.
4. Patients testing smear positive for Pv will receive AL, at one site and CQ at the other site. After G6PD testing results are available, the patients not found to be G6PD deficient will be randomized to either AL alone or AL+PQ at one study site and CQ alone or CQ+PQ at the other site. Those found to be G6PD deficient will remain in either the AL or CQ alone arms. The study will not be blinded, although microscopists reading blood films will not be aware of which arm a participant is from.
5. On day 0, each patient will receive the morning dose of treatment (AL or CQ) medication under direct observation and will be monitored for vomiting for 60 minutes. The patient or parent will be given the evening dose (for AL only) to administer at home. Each patient will return on days 1 and 2 (and up to 14 days for those in the PQ arms) for subsequent doses. Those in the primaquine arms will return on every second day on days 2-16 for directly observed therapy. Clinical reassessments will be made on days 1- 3, 7, 14, 21, 28, 35, 42, and then monthly (see Annex V and VI for a table of scheduled procedures).

Participants will be given 35 Ethiopian Birr for each visit to cover their travel expenses (this is

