#### **Safety end points**

Change in hemoglobin concentration within 7 days of start of treatment in PQ compared to the no PQ arm. Hemoglobin concentration will be assessed on day 0, 3, 7, 14, 28, 42. All adverse events will be documented. The proportion of participants with solicited and unsolicited adverse events, overall and specific, will be compared between treatment arms. Events will be analysed in relation to time of the drug administration.

The classification of treatment outcomes will be based on an assessment of the parasitological and clinical outcome of antimalarial treatment according to the latest guidelines from WHO [41].

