### **Day 1:**

---

Clinical assessment — referral in case of severe malaria/danger signs  
Measurement of axillary temperature  
Parasitological assessment  
G6PD testing and randomization if G6PD normal  
Treatment, second dose or alternative treatment in case of early treatment failure

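### The main haemoglobin safety comparison does not condition on the day-0 value, which costs some precision but does not introduce bias

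*Protocol*

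**What the plan says.** The Phase 1 safety objective in the Protocol is "To compare changes in hemoglobin concentration following vivax infection in patients receiving PQ versus patients who" do not receive it. The Safety end points section makes this specific: "Change in hemoglobin concentration within 7 days of start of treatment in PQ compared to the no PQ arm". The same section gives the measurement days: "Hemoglobin concentration will be assessed on day 0, 3, 7, 14, 28, 42".

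The list of final analyses in the Data analysis plan covers haemoglobin in one line: "Comparison in absolute means and relative changes in hemoglobin concentration during follow-up after treatment". It names no test, model or covariate, and does not say which of the two contrasts answers the objective.

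Two design facts bear on the point. In Annex VI, PQ allocation falls on Day 1: "G6PD testing and randomization if G6PD normal". Under Laboratory Evaluations, patients are "randomized to either AL alone or AL+PQ at one study site and CQ alone or CQ+PQ at the other site", and those found G6PD deficient stay on AL or CQ alone without entering that randomisation.

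**The concern.** Day-0 haemoglobin is collected from every patient and precedes the PQ randomisation, so it is a valid baseline covariate. Neither listed contrast conditions on it. Absolute means leave it out. Relative change divides by it, which uses the value but is not the same as adjusting for it.

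The population makes this relevant. Patients enter from just over one year of age with no stated upper limit, and with any haemoglobin of at least 8 g/dL. Stable differences between patients therefore pass in full into the variance of raw means, whereas adjustment removes the part that day 0 predicts.

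At stake is the width of the interval around the PQ effect on haemoglobin. The sample size was set on day-42 efficacy alone. No standard deviation, power or detectable difference is given for haemoglobin, so the choice of analysis is a free way to sharpen the safety answer.

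**Working it through.** **The plan's own figures.** The only sample-size figures concern efficacy. The inputs are 68% success ("CQ alone showed a success rate of 68% at day 42") against 87% with PQ, at 90% power. With p̄ = 0.775, the pooled two-sided formula is n = [z_α √(2p̄(1−p̄)) + z_β √(p₁(1−p₁) + p₂(1−p₂))]² / (p₁−p₂)².

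- At alpha 0.025: (2.241 × 0.5906 + 1.282 × 0.5751)² / 0.0361 = 117.6, so 118 per group, as stated.
- At alpha 0.05 the stated 97 is obtained with the unrounded 1 − 0.4 × 0.32 = 0.872. The rounded 0.87 gives 100.

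Neither figure says anything about haemoglobin.

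**Inputs for haemoglobin.** The documents supply 120 enrolled per arm. They supply no correlation ρ between day-0 and follow-up values, so ρ from 0.3 to 0.9 is assumed, with equal standard deviations at both times and a linear relation.

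**Formulas.** Large-sample variance of the difference between arms, in units of 2·SD²/n:

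- follow-up means: 1
- absolute change from day 0: 2(1 − ρ)
- adjusted for day 0 (ANCOVA): 1 − ρ²

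The ratio of ANCOVA to raw means is 1 − ρ². The ratio of ANCOVA to change is (1 − ρ²) / [2(1 − ρ)] = (1 + ρ)/2.

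| ρ | Raw | Change | ANCOVA | ANCOVA/raw | ANCOVA/change | Saving against the better of the two |
|---|---|---|---|---|---|---|
| 0.3 | 1 | 1.4 | 0.91 | 0.91 | 0.65 | 9% (raw better) |
| 0.5 | 1 | 1.0 | 0.75 | 0.75 | 0.75 | 25% (equal) |
| 0.7 | 1 | 0.6 | 0.51 | 0.51 | 0.85 | 15% (change better) |
| 0.8 | 1 | 0.4 | 0.36 | 0.36 | 0.90 | 10% (change better) |
| 0.9 | 1 | 0.2 | 0.19 | 0.19 | 0.95 | 5% (change better) |

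Interval width scales with the square root. Against the better contrast, √0.91 = 0.954, √0.75 = 0.866 and √0.95 = 0.975, so intervals are about 3% to 13% narrower.

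**Detectable difference.** At 90% power, two-sided 0.05 and 120 per arm, (1.960 + 1.282) × √(2v/120), in SD units:

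| ρ | Raw | Change | ANCOVA |
|---|---|---|---|
| 0.5 | 0.418 | 0.418 | 0.362 |
| 0.7 | 0.418 | 0.324 | 0.299 |
| 0.8 | 0.418 | 0.265 | 0.251 |

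**Relative change.** The formulas above are for absolute change, while the plan lists relative change, so this was simulated: 4,000 runs, 108 per arm, with an illustrative mean of 12 g/dL, SD 1.5 and true difference 0.5 g/dL. Power was:

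| ρ | Raw | Absolute change | Relative change | ANCOVA |
|---|---|---|---|---|
| 0.5 | 0.67 | 0.68 | 0.67 | 0.80 |
| 0.7 | 0.69 | 0.89 | 0.88 | 0.93 |
| 0.8 | 0.70 | 0.97 | 0.97 | 0.98 |

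Relative change behaves almost exactly like absolute change here.

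**Chance imbalance.** Suppose the PQ arm starts d g/dL higher by chance. Given d, the raw-mean contrast is offset by ρd and the change contrast by ρd − d = −(1 − ρ)d. At ρ = 0.5 these are +0.5d and −0.5d, so the two types of contrast can pull in opposite directions in a given trial. Both offsets average to zero over repeated randomisation. Conditioning on day 0 removes them.

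**The case against.** The strongest reply is that the quoted line is one item in a list of outputs. It does not call the comparisons unadjusted, it fixes no model, and the choice of covariates is often left to a statistical analysis plan. A comparison of means can be reported from an adjusted model, and the protocol does not rule that out. This stands as a reason to rate the point low. It does not remove the point, because the section presents itself as the statistical methodology and names the contrasts. An analysis that followed them literally would use the less efficient forms.

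Three stronger readings are tempting, and the documents do not support them.

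- A reader might infer that the planned analysis ignores the baseline altogether. It does not: relative change and the 7-day change endpoint both use day 0. Only the absolute-means output leaves it out.
- A reader might infer that the planned contrasts are biased, or would more often mistake chance for haemolysis. Among randomised patients they are unbiased and hold the nominal false-positive rate, as the adjusted analysis does. Adjustment gains precision and protects against an imbalance actually observed.
- A reader might take the largest single ratios as the loss: 81% of the variance against raw means at ρ = 0.9, or 35% against change at ρ = 0.3. Each is measured against the worse of the two contrasts at that correlation.

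It is also fair to say that haemolysis is not judged by this contrast alone. Anaemia is tabulated by arm, and falls above 2.4 g/dL lead to G6PD genotyping.

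**Conclusion.** The point holds as one of efficiency. The listed haemoglobin contrasts are valid among randomised patients but never more precise, in large samples, than a comparison adjusted for day 0. The variance saving against the better of raw means and absolute change is about 5% to 25% for ρ between 0.3 and 0.9. It peaks near ρ = 0.5 and shrinks at high correlation, where change from day 0 already does most of the work.

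The size rests on an assumed ρ, equal standard deviations and a linear relation. The simulated mean, SD and effect are illustrative only. Importance is low: a worthwhile refinement of the only named safety objective, not an error that threatens the result.

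The validity statement covers randomised patients only. G6PD-deficient patients remain in the no-PQ arms without being randomised, and day-0 adjustment does not make them comparable.

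**What to change.** Add one sentence to the Data analysis plan:

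*The main haemoglobin safety comparison is a linear model of day-7 haemoglobin on PQ assignment, with day-0 haemoglobin and site/partner drug as covariates, among randomised G6PD-normal patients, reported as the adjusted difference in g/dL with its 95% confidence interval.*

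Day 7 closes the window set in the Safety end points section, so no new outcome is introduced. Absolute means and relative changes, including those at the other visits, stay as descriptive summaries. G6PD-deficient patients are shown separately.

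The Laboratory Evaluations section ties partner drug to site, so one factor covers both. If allocation to AL or CQ is instead randomised within site, as the treatment section can be read, site and partner drug enter as two factors.

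The cost is this wording. It needs no extra visits, samples or patients.

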#### Phase2:

- 1) **Efficacy:** To measure the clinical and parasitological efficacy of AL vs. AL+PQ, or CQ vs. CQ+PQ among patients  $\geq 12$  months of age suffering from uncomplicated vivax malaria by determining the number of recurrent vivax episodes (symptomatic as well asymptomatic) in patients receiving PQ versus patients who don't receive PQ during a 12 month follow up period.

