### For Primaquine:

- Number of vivax episodes following initial parasite clearance during the follow-up period.

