#### **Criteria for withdrawal/protocol violation**

Patients meeting any of the following criteria will be withdrawn:

- Withdrawal of consent
- Failure to complete the treatment
- Vomiting both initial and replacement doses at any single time in the treatment (i.e. If the patient vomits both attempts to administer the morning dose that would require withdrawal; however, vomiting the initial morning dose but not the morning replacement dose would not require withdrawal), persistent vomiting
- Severe side-effects necessitating hospitalization
- Progression to severe malaria
- Occurrence during the follow-up of concomitant disease that would interfere with a clear classification of the treatment outcome
- Antimalarial (or antibiotics with antimalarial activity) treatment administered by a third party or self-medication with antimalarial (or antibiotics with antimalarial activity- Annex IV) assessed by asking participants or their caretaker at follow-up visits
- Erroneous inclusion of a patient outside of the inclusion/exclusion criteria
- Misclassification of a patient due to a laboratory error (parasitemia) leading to the administration of the rescue treatment

Patients who are withdrawn will be followed up if possible and will be censored or excluded from the analysis. The reasons for discontinuation or protocol violation will be recorded on the case report form.

**Training for personnel:** Clinicians and laboratory personnel are trained and licensed in Ethiopia. In addition, they will receive approximately 1 week additional training to review the protocol of this study. In addition to technical aspects of specific laboratory techniques and clinical assessments, training will stress the importance of confidentiality, and appropriate techniques for obtaining informed consent. Continued appropriate processes with regard to informed consent will be reinforced by intermittent observation by the supervisor. The staff will include 1-2 laboratory technicians for microscopy, and 1-2 staff persons for enrollment and clinical assessments.

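### The 12-month recurrence endpoint is compared as a bare number of episodes with no observed-time denominator, and neither stated drop-out rule suits such a count

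*Protocol*

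**What the plan says.** The Phase 2 objective measures efficacy over 12 months "by determining the number of recurrent vivax episodes (symptomatic as well asymptomatic", PQ against no PQ. The outcome definition for primaquine, repeated in Annex I, is "Number of vivax episodes following initial parasite clearance during the follow-up period". The Study Design section likewise says that numbers of relapses will be compared between arms. The matching line in the data analysis plan is "Comparison of number of recurrent parasitological vivax episodes after initial parasite episode". None of these places mentions time at risk or a rate.

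The same section opens with two methods for the data in general: a per-protocol analysis, "where patients who were withdrawn from the study or who were lost to follow-up are excluded", and a survival analysis, "where all enrolled patients are included in the analysis until the last day before drop-out". The withdrawal section adds: "Patients who are withdrawn will be followed up if possible and will be censored or excluded from the analysis". Both methods are expressly attached to one output only: "The proportion of treatment failures in each Pv arm at day 28 and day 42 with 95% confidence intervals using both methods of analysis".

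The only loss figure is in the sample size section, for the day-42 comparison: "Taking into account 10-20% loss to follow-up at 42 days", leading to 120 patients per treatment.

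**The concern.** Recurrences are detected from slides at study visits, so a patient who leaves at month 3 has had about a quarter of the opportunity of one who stays for 12 months. A number of episodes is comparable between arms only if observed time is equal or enters the analysis. The protocol expects losses within the first six weeks of a one-year follow-up, yet gives the count no denominator.

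The recurrence count is the only Phase 2 efficacy objective, and it is meant to inform national policy on primaquine. At stake are precision (observed months thrown away), the absolute burden of recurrence per patient-year, and the PQ versus no-PQ ratio wherever leaving the study is related to arm or to recurrence.

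**Working it through.** The protocol states no figure for the 12-month endpoint, so there is none to reproduce. The check is a reading of the rules, then conditional illustrations.

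**1. Two readings of the analysis section.**
- *The two methods do not govern the recurrence line* (they are tied by name only to day 28/42 failure). Then the count has no rule for unequal follow-up.
- *They do govern it.* Then per protocol deletes lost and withdrawn patients entirely. With 120 per arm and 10-20% lost by day 42, that is 120 × 0.10 = 12 to 120 × 0.20 = 24 patients per arm before later losses, and a patient lost at month 10 contributes nothing. The survival method keeps them to drop-out, but no recurrent-event or rate method is named, so a number of episodes does not follow from it.

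**2. Is the exclusion neutral?** Three of the protocol's rules suggest not.
- Patients count as withdrawn if PCR is unclassifiable. The genotype comparison is made on recurrent parasitaemia, so only patients with a recurrence can be removed this way.
- Self-medication or third-party antimalarials, and progression to severe malaria, are withdrawal criteria. Both are plausibly commoner in patients with more episodes.
- Not completing treatment is a withdrawal criterion. The course lasts 14 days with PQ and 3 days without, and the End-points section has each recurrence treated again as allocated, so exposure to this rule differs by arm.

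**3. Loss unrelated to recurrence.** Assume that all enrolled patients are the denominator, that a share L is lost by day 42 at a mean of day 21, and that nobody is lost later. Observed fraction = L × 21/365 + (1 − L).
- L = 0.10: 0.906, so 9.4% of person-time is missing. L = 0.20: 0.812, so 18.8% is missing.
- A further 10-30% lost evenly over days 42-365: 13-30% missing.
- 10-20% in total, spread evenly over 12 months: 5-10% missing.
- The 42-day hazard λ = −ln(1 − L)/42 continued to day 365, observed fraction (1 − e^(−365λ))/(365λ): 35-56% missing.

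The result depends almost wholly on the assumptions. In the between-arm ratio, equal loss gives a factor of 1.00. Loss of 20% in one arm and 10% in the other gives 0.812/0.906 = 0.90, or 1.12 the other way round.

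**4. Exclusion triggered by an episode (all inputs assumed).** Mean rates μ = 2.0 (no PQ) and 0.8 (PQ) per year, gamma frailty with variance 1, each episode carrying chance p of exclusion. The mean count among patients kept is μ(1 − p)/(1 + μp).
- p = 0.05: 1.90/1.10 = 1.73 and 0.76/1.04 = 0.73; ratio 0.42.
- p = 0.10: 1.80/1.20 = 1.50 and 0.72/1.08 = 0.67; ratio 0.44.
- p = 0.20: 1.60/1.40 = 1.14 and 0.64/1.16 = 0.55; ratio 0.48.

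The true ratio is 0.40, so the benefit of PQ is understated.

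**5. Drop-out that rises with recurrence (all inputs assumed).** Same rates and frailty; yearly drop-out hazard 0.10 + 0.15 × individual rate; 30% (no PQ) and 19% (PQ) lost by 12 months.
- Completers: μ/(1 + 0.15μ) = 2.0/1.30 = 1.54 and 0.8/1.12 = 0.71; ratio 0.46.
- Raw count per enrolled patient, integrated over the frailty: 1.470 and 0.681; ratio 0.46.
- Episodes per observed year: 1.470/0.834 = 1.76 and 0.681/0.900 = 0.76; ratio 0.43.

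Person-time roughly halves the error. On the unrounded ratios 0.463 and 0.429, (0.429 − 0.400)/(0.463 − 0.400) = 46% of it remains.

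**The case against.** A reader might infer that time after drop-out is counted as recurrence-free and that rates are therefore 9-19% too low on the protocol's own loss figure. The documents do not support that. No section keeps lost patients in the denominator with 12 months' credit; the withdrawal and analysis sections exclude or censor them. The 10-20% is a 42-day allowance for sizing the day-42 comparison. Turning it into 9-19% over a year needs an all-enrolled denominator, mean loss at day 21 and no later loss.

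It is also fair to say that the planned analysis is a comparison, in which equal loss cancels. Nothing in the protocol predicts 10% loss in one arm and 20% in the other, and phone calls, home tracing and travel payments all work against loss. Follow-up to the last day before drop-out is the time-at-risk rule that a rate analysis needs. The choice of model and offset is commonly left to an analysis plan, and the one for this trial, if it exists, is not shown.

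All of that stands against the larger claim. It does not answer the narrower one. The protocol does more than leave a detail open: it defines the outcome as a count throughout and prescribes, for the data in general, an exclusion rule that discards observed follow-up and selects on post-randomisation events.

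**Conclusion.** The point holds in a limited form. The 12-month endpoint is a number of episodes without observed time, and the two stated methods serve it badly: one discards follow-up already observed, and the other does not by itself yield a count.

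No fixed percentage of understatement can be claimed. If loss is equal and non-informative, the between-arm ratio is unbiased, and exclusion costs precision only. If loss differs by arm or follows recurrence, the ratio is biased. Under the assumed inputs shown, a true 0.40 becomes 0.42-0.48 with episode-triggered exclusion and about 0.46 with raw or completers-only counts. Those figures rest on assumed rates, frailty and drop-out, not on protocol data. The day 28/42 failure proportions are a separate output that this point does not touch. The change should be made because the sole Phase 2 efficacy objective depends on this comparison.

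**What to change.** In the data analysis plan, replace the last item of the list of final analyses with wording such as:

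*Incidence of vivax recurrence per person-year of observed follow-up, from first parasite clearance to last slide. All patients randomised to PQ or no PQ are included up to their last slide. PQ is compared with no PQ within each partner drug by a count model that allows overdispersion (for example negative binomial), with log observed time as offset.*

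State that the per-protocol exclusion does not apply to this main analysis, and keep a per-protocol or completers-only count as a sensitivity analysis. Add a sentence that a person-time rate reduces bias from informative drop-out but does not remove it, so losses and reasons for withdrawal should be read by arm alongside the result.

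The cost is wording only. Visit dates and slide results are already collected, and no extra patients, visits or samples are needed.
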